### Target sample size and statistical analyses

The reported CR rates have ranged from 11 to 25%. In this study, we estimate a rate of 20% as the CR threshold. Therefore, we calculated the sample size of the primary locally advanced ESCC part at 38 with a CR of 40% deemed promising and one of 20% deemed unacceptable (one-sided α, 0.05; β, 0.2). Under this calculation, we are planning to include a maximum of 40 patients in the primary locally advanced ESCC part. We set the planned sample size of the postoperative locoregionally recurrent ESCC part at a maximum of 10 patients in an exploratory manner. We will calculate the confirmed CR by the investigator’s assessment and its 90% confidence interval using the exact binomial method. The results will be considered statistically significant with more than 13 confirmed CR cases in accordance with both the RECIST and the Japanese Classification of Esophageal Cancer in the primary locally advanced ESCC part (i.e., CR rate ≥ 34.2%). We will also determine the confirmed CR rate by central assessment, the ORR by the investigators’ assessment, the PFS, and the OS using appropriate statistical methods. Finally, we will also tabulate the incidence of AEs in the safety population.

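### The success rule contradicts itself at exactly 13 complete responses, and read literally it misses the stated 80% power

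*Protocol article*

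**What the plan says.** All the relevant text is in the protocol article, section *Target sample size and statistical analyses*.

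- **Design:** the primary part is sized "at 38 with a CR of 40% deemed promising and one of 20% deemed unacceptable", with error rates "one-sided α, 0.05; β, 0.2".
- **Enrolment:** "we are planning to include a maximum of 40 patients in the primary locally advanced ESCC part".
- **Estimate:** the confirmed complete response (CR) rate by investigator assessment is reported with "its 90% confidence interval using the exact binomial method".
- **Decision rule as a count:** "The results will be considered statistically significant with more than 13 confirmed CR cases".
- **Decision rule as a rate, offered as its equivalent:** "i.e., CR rate ≥ 34.2" per cent.

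The *Discussion* makes a confirmatory phase III trial depend on a significant improvement in the confirmed CR rate.

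**The concern.** The count and the rate are presented as one rule in two forms, but they describe different rules at the planned size of 38. The rate is also tied to 38 although enrolment may reach 40, so its meaning in patients changes with the final number. In addition, the plan specifies a one-sided 5% test and an exact 90% interval, which together imply a boundary of their own.

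This is the only success criterion for the primary endpoint, and it feeds the phase III decision. If the trial ends with 13 confirmed CRs, someone must choose between the readings after seeing the data. The literal count rule is also stricter than the rule that supports the sample size, so the power claimed for 38 patients would not be delivered.

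**Working it through.** **Inputs (all from *Target sample size and statistical analyses*).** p0 = 0.20, p1 = 0.40, one-sided α = 0.05, β = 0.20, planned n = 38, maximum n = 40.

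**Formulas.** With X ~ Binomial(n, p) and success at r or more CRs:

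- attained α = P(X ≥ r | n, 0.20)
- power = P(X ≥ r | n, 0.40)
- the exact (Clopper-Pearson) lower 90% limit L for x CRs solves P(X ≥ x | n, L) = 0.05, so L = Beta⁻¹(0.05; x, n − x + 1)

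It follows that L > 0.20 exactly when P(X ≥ x | n, 0.20) < 0.05. The lower 90% limit and the one-sided 5% exact test give the same verdict.

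**Step 1: reproduce the plan's 38.** At n = 38, r = 12 gives α = 0.0623, which is too large. r = 13 gives α = 0.0288 and power 0.8136. The critical count is therefore 13, and 38 patients meet the stated errors. Exact power first reaches 80% at n = 35 but drops to 77.8% at n = 37. From n = 38 it stays at or above 80% at every size checked (up to 59). The design figure is sound when success means 13 or more.

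**Step 2: compare the two forms of the rule.** 13/38 = 34.21% and 14/38 = 36.8%. The rate threshold is thus 13 or more of 38, while the count threshold is 14 or more. At larger n the rate threshold needs 0.342 × 39 = 13.3, hence 14 patients, and 0.342 × 40 = 13.7, hence 14.

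**Step 3: verdicts when exactly 13 CRs are observed.**

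| n | Observed rate | Count rule (>13) | Rate rule (≥34.2%) | Exact one-sided p | Exact 90% CI | Excludes 20%? |
|---|---|---|---|---|---|---|
| 38 | 34.2% | fails | passes | 0.0288 | 21.6% to 48.8% | yes |
| 39 | 33.3% | fails | fails | 0.0355 | 21.0% to 47.7% | yes |
| 40 | 32.5% | fails | fails | 0.0432 | 20.4% to 46.6% | yes |

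**Step 4: operating characteristics of each reading.**

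| n | Success at | Attained α | Power at 40% |
|---|---|---|---|
| 38 | ≥13 | 0.0288 | 81.4% |
| 38 | ≥14 | 0.0120 | 71.0% |
| 39 | ≥13 | 0.0355 | 84.5% |
| 39 | ≥14 | 0.0154 | 75.2% |
| 40 | ≥13 | 0.0432 | 87.1% |
| 40 | ≥14 | 0.0194 | 78.9% |

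Twelve CRs do not reject at 39 (α = 0.0742) or at 40 (α = 0.0875), so the exact critical count is 13 at all three sizes.

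**Step 5: how often the ambiguity would matter.** P(X = 13) is the difference between adjacent tails. Under 40% it is 0.8136 − 0.7103 = 10.3% at n = 38 and 0.8715 − 0.7888 = 8.3% at n = 40. Under 20% it is 0.0288 − 0.0120 = 1.7% and 0.0432 − 0.0194 = 2.4%.

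**The case against.** The best defence is that this is a slip of wording. At n = 38 the sample size calculation, the printed 34.2% and the exact interval all point to 13 or more, and only the words *more than* are out of line. That is probably how the error arose. It makes the repair easy, but the literal sentence still gives the opposite verdict at 13.

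Three further points limit the finding.

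- **The interval is not declared a decision rule.** The article says only that it will be calculated. This is correct, but its lower limit is equivalent to the one-sided 5% exact test that the design specifies, so the conflict is with the plan's own test.
- **At 39 and 40 the count and rate rules agree, since both need 14.** This is also correct. At those sizes the rule is stricter than the stated test requires, which is conservative rather than contradictory in itself. The 78.9% power at 40 is only about one point below target; the material loss is 71.0% at 38.
- **The false-positive risk is never inflated.** Attained α lies between 0.012 and 0.043 under every reading, and the dispute concerns one outcome in a single-arm proof-of-concept trial.

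The choice of analysed denominator may properly sit in the full protocol or analysis plan. That does not repair a count and a rate that are stated here as equivalent and are not.

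**Conclusion.** The concern holds. As written, the primary decision rule is internally contradictory at 13 of 38. At 39 and 40 it is stricter than the one-sided 5% test on which the design rests. Requiring 14 or more gives power of 71.0%, 75.2% and 78.9% at 38, 39 and 40, all below the stated 80%; the shortfall is serious at 38 and marginal at 40. The reading of 13 or more is the one that supports the planned 38. It keeps α below 0.05 and power above 80% at all three sizes.

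The harm is an undetermined conclusion at one result (probability 10.3% at 38 or 8.3% at 40 if the true rate is 40%) and lost power, not inflated type I error. The figures assume an exact binomial test, a true CR rate of exactly 20% or 40%, and 38 to 40 analysed patients. Because this is the sole success criterion and it leads to phase III planning, it should be corrected before the primary analysis.

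**What to change.** Replace the decision sentence, in the protocol and in the analysis plan, with wording such as:

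> The null hypothesis of a CR rate of 20% or less is rejected if the lower limit of the exact 90% confidence interval exceeds 20%. This corresponds to 13 or more confirmed CRs among 38, 39 or 40 analysed patients (13/38 = 34.2%; 13/40 = 32.5%).

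Remove the strict inequality on 13 and the single fixed threshold of 34.2%. State the attained operating characteristics: α 0.029 and power 81% at 38, and α 0.043 and power 87% at 40. If the analysed number falls outside 38 to 40, the confidence-limit form governs, because the critical count can change (it is 12 at 36 and 14 at 41).

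The cost is one sentence in each document. No extra patients or data are needed.

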### Biomarker analyses and translational research

We will perform serial biopsies from the primary site and blood collections at 3 time points (before CRT, after CRT, and four weeks after the first atezolizumab dose). Using the collected samples, we will investigate biomarkers for efficacy or resistance to the sequential combination of CRT and atezolizumab. We will also analyze whole exome sequencing, neoantigens, microsatellite instability, tumor mutational burden, phenotype of immune-competent cells using both flowcytometry and immunohistochemistry, PD-L1 status, and Human Leukocyte Antigen haplotyping.

## Discussion

The TENERGY trial is the first phase II POC study to evaluate the efficacy and safety of sequential combination therapy with 1 year of atezolizumab following definitive CRT in patients with unresectable locally advanced ESCC. The synergistic efficacies of CRT plus ICIs combination should improve the confirmed CR rate, resulting in a prolonged survival. If the combination significantly improves the confirmed CR rate, we will plan a confirmatory phase III trial. Also, as the incidence of T4b esophageal cancer is estimated approximately at 1500 patients per year in Japan, we expect the Japanese Accelerated Approval Program will allow for earlier approval of drugs that treat serious conditions, and that fill an unmet medical need.

Moreover, because CRT is one of the standard treatment options for patients with early stage to locally advanced ESCC, the application of sequential combinations of CRT plus ICIs should be potentially expandable to patients with all ESCC stages and the results of our trial may guide standard ESCC treatment modifications.

## Data Availability

The datasets used and/or analyzed during the current study are available from the corresponding author on reasonable request.

## Abbreviations

CRT: Chemoradiotherapy
CR: Complete response
OS: Overall survival
ICIs: Immune checkpoint inhibitors
PD-1: Programmed death 1
PD-L1: Programmed death ligand 1
CPS: Combined positive score
ESCC: Esophageal squamous cell carcinoma
FDA: Food and Drug Administration
MHC: Major histocompatibility complex
IFN-γ: Interferon gamma
PFS: Progression-free survival
POC: Proof-of-concept
ORR: Objective response rate
AEs: Adverse events
CT: Computed tomography
RECIST: Response Evaluation Criteria in Solid Tumors
PR: Partial response
CTCAE: Common Terminology Criteria for Adverse Events
